### Secondary outcomes

#### Socio-demographic and clinical information

Demographic and other health information will be collected using a questionnaire. This anamnesis will include questions regarding smoking and alcohol habits, history of illness (as osteoporosis, CVD, hypertension, diabetes), menopause status, indicators of socio-economic status (such as personal and household income, education level…), marital status, and number of children. The pharmacology register as well as the number and reason of medical visits will be consulted by the primary care medical staff in collaboration with members of the research team through the medical database.

Systolic and diastolic blood pressure, as well as resting heart rate, will be measured after 5 min of rest, on 2 separate occasions (with 2 min between trials), with the person seated (Omron Health Care Europe B.V. Hoolddorp). The lowest value of the two trials will be selected for the analysis.

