**Methods/Design:**

The present study is a Randomized Controlled Trial.

A total of 150 eligible women will be recruited and randomly assigned to either a 16-week exercise intervention (3 sessions/week), or to usual care (control) group.

The primary outcome measure is the incremental cost-effectiveness ratio. The secondary outcome measures are: i) socio-demographic and clinical information; ii) body composition; iii) dietary patterns; iv) glycaemic and lipid profile; v) physical fitness; vi) physical activity and sedentary behaviour; vii) sleep quality; viii) quality of life, mental health and positive health; ix) menopause symptoms. All outcomes will be assessed at baseline and post intervention. The data will be analysed on an intention-to-treat basis and per protocol. In addition, we will conduct a cost effectiveness analysis from a health system perspective.

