### Sample size

The number of participants to be included in the study was calculated on the basis of the change in quality of life as assessed with the *EuroQol 5D (*EQ-5D-5 L). To the best of our knowledge, there is no available data regarding group differences in changes in quality of life following any type of intervention in middle aged women. Therefore, we assumed a difference of 0.07 units as clinically meaningful based on previous observations from our group (unpublished observations). Therefore, a total of 124 participants (62 per group) is needed to detect a mean group difference of 0.07 and a standard deviation of 0.12 in the total EQ-5D score with a power of 90 % and α of 0.05. However, we will attempt to exceed this sample size to allow for withdrawals. Assuming a maximum lost-to-follow up of 20 %, a minimum of 75 participants per group will be recruited (*n* = 150).

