### Statistical analysis

Baseline characteristics of the study participants will be presented as mean (standard deviation) for continuous variables and proportions for categorical variables.

Statistical analysis will be performed on the intention to treat population, thus including all randomized participants (in the groups to which they were randomly assigned) in the analysis. Missing data will be replaced using multiple imputations. The effects of the intervention on the primary and secondary outcomes will be assessed with repeated measures analysis of covariance adjusted for age and baseline values. The effect size (95 % confidence interval) and statistical significance will be reported for each study outcome with regards to the main group (between-subjects) time (within-subjects) and their interaction (group × time) effects. The statistical significance will be set at the conventional level of p<0.05. To account for potential estimations biases or inefficiency, sensitivity analyses will be undertaken using baseline observation carried forward imputation, and also the available case population (participants who actually received the treatment; i.e. no imputations).

*Ancillary analyses.* "Per-protocol" analyses will also be performed on participants with overall ≥75 % treatment compliance.

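### Blood pressure and resting heart rate are analysed as the lower of two readings; the mean of the same two readings would be more precise at no cost

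*Protocol article*

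**What the plan says.** The rule is in the protocol article under Secondary outcomes, Socio-demographic and clinical information. It covers three variables: "Systolic and diastolic blood pressure, as well as resting heart rate". They "will be measured after 5 min of rest, on 2 separate occasions (with 2 min between trials), with the person seated". The next sentence fixes what enters the analysis: "The lowest value of the two trials will be selected for the analysis".

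The abstract gives these variables outcome status: "The secondary outcome measures are: i) socio-demographic and clinical information". It also says that all outcomes are assessed at baseline and post intervention. The Statistical analysis section says that effects on primary and secondary outcomes "will be assessed with repeated measures analysis of covariance adjusted for age and baseline values". The lower reading therefore serves both as the outcome and as the baseline covariate.

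No other section gives a reason for the rule, replaces it, or mentions averaging these readings.

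**The concern.** Two readings are taken and one is discarded according to its value. This has two consequences.

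- **Level.** The lower of two noisy readings is on average below their mean, by an amount that grows with reading-to-reading variability. Reported absolute values are shifted down accordingly.
- **Precision.** The lower reading varies more from one repetition to another than the mean of the pair does. That extra noise enters the residual variance of the comparison between arms.

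At stake is some precision for three cardiovascular variables, and a reported level that depends partly on measurement noise. The primary outcome is not involved.

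**Working it through.** **Inputs.** From the article: two readings per visit, 2 min apart, with the minimum analysed. The article gives no SD for blood pressure or heart rate, and no figure on this point to reproduce. The only SD used for planning belongs to the EQ-5D score ("a total of 124 participants (62 per group) is needed to detect a mean group difference of 0.07 and a standard deviation of 0.12") and plays no part here. Assumed: independent, roughly normal reading errors with the same SD s around the woman's level at that visit. Any error shared by both readings counts as other variation.

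**Step 1: level and error variance, in units of s.**

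| Summary of two readings | Expected shift | Error variance |
|---|---|---|
| Minimum | −s/√π = −0.564 s | s²(1 − 1/π) = 0.682 s² |
| Mean | 0 | s²/2 = 0.500 s² |

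Variance ratio: 0.682/0.500 = 1.36. Error-SD ratio: √1.36 = 1.17. A simulation of 2,000,000 pairs agreed (shift −0.564, variances 0.682 and 0.499).

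**Step 2: a settling effect.** A second reading is often lower than the first. Simulated with a systematic fall from first to second reading:

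| Fall | Minimum below mean by | Variance ratio |
|---|---|---|
| 0.25 s | 0.57 s | 1.38 |
| 0.5 s | 0.60 s | 1.41 |
| 1 s | 0.70 s | 1.52 |
| 2 s | 1.05 s | 1.79 |

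The loss of precision grows with the fall.

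**Step 3: the shift in mmHg (assumed s, no settling).**
- s = 3: 3 × 0.564 = 1.7 mmHg
- s = 8: 8 × 0.564 = 4.5 mmHg

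**Step 4: effect on total variance.** Let T be the SD of all other variation. The ratio is (T² + 0.682 s²)/(T² + 0.500 s²). An assumed T of 7 mmHg stands for residual variation after adjustment. An assumed T of 10 to 15 mmHg stands for variation between women.

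| s | T | Calculation | Ratio |
|---|---|---|---|
| 3 | 15 | 231.1/229.5 | 1.007 |
| 5 | 10 | 117.0/112.5 | 1.040 |
| 8 | 10 | 143.6/132 | 1.088 |
| 4 | 7 | 59.9/57 | 1.051 |
| 6 | 7 | 73.5/67 | 1.098 |
| 8 | 7 | 92.6/81 | 1.144 |

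The excess is about 1 to 14 %. Confidence intervals widen by the square root: √1.007 = 1.004 to √1.144 = 1.07, so by about 0.4 to 7 %.

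This counts only noise in the outcome. The baseline covariate is also noisier under the minimum, and that is not included.

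**The case against.** The strongest defence is that the rule is prespecified, unambiguous and the same in both arms and at both visits. Assessors and analysts are blinded, and the analysis adjusts for baseline. Nothing is contradicted. This stands: the point is an improvement to an analysis choice and does not correct an error.

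A second defence is that bias presupposes a target. If the first reading is raised because the woman has not settled, the mean is itself too high as a measure of resting level. This stands in part. Once the fall exceeds about 0.6 s, the minimum is on average closer to the settled level than the mean is. The shift is therefore described here only relative to the expected mean of the two readings. The article states no such rationale, and Step 2 shows that the minimum stays noisier in that situation.

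A third defence is that taking the best of two attempts is the article's convention for handgrip strength, flexibility and the timed up and go test. There, best performance is the quantity of interest. A seated resting measurement is not a performance test, so the convention does not carry over.

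A reader might also infer three stronger harms, which the article does not support:

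- **A spurious difference between arms.** If within-visit SD differed by arm, the rule would create a difference of (s₁ − s₂)/√π, for example (6 − 5) × 0.564 = 0.56 mmHg. Nothing in the article suggests that training changes variability between readings 2 min apart. With s = 6 and T = 7, the residual SD is √73.5 = 8.6 mmHg. The standard error of the arm difference is then about 1.4 to 1.5 mmHg with 75 to 62 women per arm, so even this invented artefact is about 0.4 of one standard error.
- **Under-counting of raised blood pressure.** The article nowhere classifies measured pressure. Hypertension is collected as history of illness.
- **Distorted links with costs.** The objectives in the Background do not name blood pressure among the variables to be related to costs, and a roughly constant shift would not change an association.

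**Conclusion.** The concern holds as a minor point about precision. Under independent, roughly normal errors with equal SD, it is certain that the minimum has 36 % more measurement-error variance than the mean and lies 0.56 s below its expected value. The shift lowers reported levels. It largely cancels between randomised arms, provided that within-visit variability is similar in both. The precision loss does not cancel.

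The practical size is small and uncertain. The range of about 1 to 14 % of total variance rests wholly on assumed SDs, and its top requires a reading error (8 mmHg) larger than all other variation (7 mmHg). No separate size was worked out for heart rate in beats per minute. The consequence is confined to a secondary outcome: the ICER, the QALYs and the sample size do not use these readings.

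**What to change.** Replace the sentence under Socio-demographic and clinical information so that the mean of the two readings is analysed for systolic pressure, diastolic pressure and resting heart rate, in the same way at baseline and post intervention. The cost is one sentence. Both readings are already scheduled, so it adds no measurement, visit or burden. The only practical requirement is that both values are recorded and kept, not just the lower one.

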#### Body composition

Lean, fat and bone mass of the whole body will be measured using a dual-energy x-ray absorptiometry (DXA) device (Hologic Discovery QDR, Nasdaq: HOLX). Height (cm) will be measured using a stadiometer (Seca 22, Hamburg, Germany). Waist circumference (cm) will be assessed at the middle point between the ribs and the ileac crest, with the participant standing (Harpenden anthropometric tape, Holtain Ltd).

#### Dietary patterns

The *Mediterranean Diet Score* [20] is an index created to evaluate the degree of adherence to the traditional Mediterranean dietary pattern. It consists of 11 items (non-refined cereals, potatoes, fruits, vegetables, legumes, fish, olive oil, red meat and derivate, poultry, full fat dairy products and alcohol), which scores ranging from 0–5 based on frequency of consumption. Thus, the total score ranges from 0–55, with higher scores indicating greater adhesion to the Mediterranean dietary pattern.

The *Food Frequency questionnaire* [21] consists on a list of 78 foods on which participants will be asked to indicate the frequency of consumption (never or number of times per day, per week, per month or per year).

#### Glycaemic and lipid profile

Venous blood samples will be collected in two vacuum tubes in standardized fasting conditions at 8–9 a.m. in the primary care centre and transported to the laboratory for subsequent analysis. One of these vacuums will contain EDTA/K3 to determine blood cells count, blood haemoglobin concentration and haematocrit. Plasma total cholesterol, high-density lipoprotein cholesterol, low-density lipoprotein cholesterol, triglycerides, glucose, insulin, albumin, glycosylated haemoglobin and thyroid-stimulating hormone levels will be assessed with standard methods using an autoanalyzer (Hitachi-Roche p800, F. Hoffmann-La Roche Ltd. Switzerland).

#### Physical fitness

Participants’ physical fitness status will be assessed by means of the following tests:

##### Cardiorespiratory fitness

The *modified Bruce protocol* [22, 23] will be performed to estimate maximal oxygen uptake (VO_2max_), and will be used as measure of cardiorespiratory fitness. The test will consist of 5 increasing workload stages of 3 min each (stage 1: 2.7 km/h and 10 % inclination; stage 2: 4 km/h and 12 % inclination; stage 3: 5.5 km/h and 14 % inclination; stage 4: 6.8 km/h and 16 % inclination; stage 5: 8 km/h and 18 % inclination). The test will conclude when the 85 % of the individual’s heart rate reserve (HRR) is accomplished. VO_2max_ will be estimated with the formula by Bruce et al. [23]: VO_2max_ = 6.70 – 2.82*2 + 0.056*duration of the test (s).

We will additionally perform the *6-min walk test*, which measures the maximum distance (in meters) each participant can walk in 6 min along a 45.7 m rectangular course [24].

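### The treadmill test stops by rule at 85 % of heart rate reserve, yet its duration is converted by a duration-only equation and labelled VO2max

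*Protocol article*

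**What the plan says.** The whole point sits in one paragraph of the protocol article, under Physical fitness, Cardiorespiratory fitness. Four statements matter:

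- **Purpose.** The treadmill test "will be performed to estimate maximal oxygen uptake (VO_2max_), and will be used as measure of cardiorespiratory fitness".
- **Structure.** "The test will consist of 5 increasing workload stages of 3 min each", so a test lasts at most 5 × 180 = 900 s.
- **Stop rule.** "The test will conclude when the 85 % of the individual’s heart rate reserve (HRR) is accomplished".
- **Conversion.** "VO_2max_ = 6.70 – 2.82*2 + 0.056*duration of the test (s", with duration in seconds. The equation is attributed to a cited reference.

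The paragraph prints no units for the result and does not say how maximal heart rate is set. It mentions no recording of heart rate by stage. No other section gives a maximal test, an extrapolation, or a different label for the value.

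The abstract lists physical fitness among the secondary outcomes ("v) physical fitness; vi) physical activity and sedentary behaviour"). Under Statistical analysis, all primary and secondary outcomes are compared between arms by repeated measures analysis of covariance, with effect sizes. In the Background, fitness also enters the two association objectives, one of which concerns costs.

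**The concern.** A maximal quantity is claimed from a test that is ended before maximum by design. If the equation's duration term means time to maximal effort, or if the equation returns the oxygen uptake reached when the treadmill stops, then the printed value is a submaximal one under a maximal name. Every second removed by the stop rule lowers the result, and no term restores it.

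What is at stake is how the published number is read. A reader would take the group means and the between-arm difference as VO2max, and might compare them with VO2max from maximal tests elsewhere. On the plan as written, that comparison is not supported.

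**Working it through.** There is no VO2max figure in the article to reproduce, so the check evaluates the stated equation and then sizes a possible shortfall.

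**1. Simplify the equation.** 6.70 − 2.82 × 2 = 6.70 − 5.64 = 1.06, so the value is 1.06 + 0.056t, with t in seconds. Duration is the only measured input. There is no heart-rate term and no term for the stopping fraction.

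**2. Evaluate it at the ends of the stages.**

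| t (s) | 1.06 + 0.056t |
|---|---|
| 180 | 11.14 |
| 360 | 21.22 |
| 540 | 31.30 |
| 720 | 41.38 |
| 900 | 51.46 |

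One second is worth 0.056 units, one minute 3.36, and one stage 0.056 × 180 = 10.08.

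**3. Size the shortfall under two assumed models.** Neither model is in the article.

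*Model A.* The equation returns the oxygen uptake at the moment of stopping, the percentage of heart rate reserve equals the percentage of oxygen-uptake reserve, and resting uptake is 3.5. The implied maximum is then (v − 3.5)/0.85 + 3.5.

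- Stop at 360 s: (21.22 − 3.5)/0.85 + 3.5 = 24.35, so the reported value is 12.8 % low.
- Stop at 720 s: (41.38 − 3.5)/0.85 + 3.5 = 48.06, so it is 13.9 % low.
- A difference between two values is reported at 0.85 of its implied size, that is 15 % too small.

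*Model B.* The duration term means time to maximal effort, and the used fraction of heart rate reserve rises linearly from f0 at the start to 1 at maximum. Then t85/tmax = (0.85 − f0)/(1 − f0), which is 0.85, 0.81 and 0.75 for f0 = 0, 0.2 and 0.4.

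| tmax (s) | Value at maximum | At the stop, f0 = 0 | f0 = 0.2 | f0 = 0.4 |
|---|---|---|---|---|
| 480 | 27.9 | 23.9 (−14.4 %) | 22.9 (−18.0 %) | 21.2 (−24.1 %) |
| 600 | 34.7 | 29.6 (−14.5 %) | 28.4 (−18.2 %) | 26.3 (−24.2 %) |
| 720 | 41.4 | 35.3 (−14.6 %) | 33.8 (−18.3 %) | 31.3 (−24.4 %) |
| 900 | 51.5 | 43.9 (−14.7 %) | 42.0 (−18.4 %) | 38.9 (−24.5 %) |

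With f0 the same in both arms and at both visits, a between-arm difference is reported at t85/tmax of its size, so it is 15 to 25 % too small (1 − 0.85 to 1 − 0.75).

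**4. What does not change.** The value is a linear function of treadmill time with a positive slope. Replacing it by time to the stop rescales outcome and baseline covariate alike. P-values, standardised effects and correlations are therefore identical for the two variables. The sample size rests on EQ-5D ("a total of 124 participants (62 per group) is needed to detect a mean group difference of 0.07 and a standard deviation of 0.12") and the primary outcome on costs and QALYs, so neither uses this value.

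**The case against.** The strongest reply is that the equation comes from a cited source that is not at hand. If that source derived it on tests ended at 85 % of heart rate reserve, the output is a proper prediction of VO2max and there is no error. An article may leave an equation's calibration to its citation, and this one speaks of estimating VO2max, not measuring it. That possibility stands, and it is why the error can be nil. But the article gives no sign that the equation was built for this stop rule, so the two statements remain unreconciled.

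The reply also has force against several stronger readings that a reader might infer:

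- *A precise bias of 13 to 14 % in the level and 15 % in the gain.* That comes from Model A alone. Model B reaches about 25 %, and calibration gives zero.
- *A fault in the trial's main fitness outcome.* The article ranks no fitness test first. It lists several, including a 6-min walk test in the same section.
- *Harm to the group comparison or to the association objectives.* Both arms share one stop rule, no bias towards either arm is shown, and step 4 shows that tests and correlations match those for treadmill time.
- *A stop point that drifts as training lowers resting heart rate.* The target is rest + 0.85 × (max − rest) = 0.85 × max + 0.15 × rest. An assumed fall of 5 beats per minute at rest moves it by 0.15 × 5 = 0.75 beats, too little to carry an argument.

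**Conclusion.** The point holds as a mismatch between stop rule, equation and label. As written, the plan turns a duration cut short at 85 % of heart rate reserve into a number called VO2max, with no correction and no statement that none is needed.

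Unless the equation was calibrated for such tests, the level is understated by roughly 13 to 25 % and the between-arm effect in VO2max units by 15 to 25 %. These ranges rest on the assumed models above and cannot be narrowed from the document.

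The consequence is limited to the scale and name of one secondary fitness variable. The comparison between arms can still be read as one of submaximal fitness. It is a minor point, worth settling before results are reported.

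**What to change.** Leave the stop rule as it is and bring equation and label into line with it:

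1. Define, analyse and report the outcome as treadmill time to 85 % of heart rate reserve, and do not call it VO2max. This uses the duration that the plan already needs. There is no need to impose one target heart rate across visits, which could itself alter the stop rule.
2. If a VO2max figure is wanted and heart rate is stored by stage, extrapolate each woman's heart-rate/workload relation to 100 % of reserve and state how maximal heart rate is set. The article does not say that heart rate is stored by stage, so this option depends on confirming it.
3. If the cited source does support the equation for tests ended at this point, one sentence saying so resolves the matter and the label can stay.

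The cost is a change of wording, an outcome scale less familiar to readers and, for the second option, a short extra derivation. The first and third options need no new measurement.

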##### Lower-body muscular strength

The *30-s chair stand test* involves counting the number of times within 30 s that the participant can rise to a full stand from a seated position with back straight and feet flat on the floor, without pushing off with the arms. The participants will perform one trial after familiarization [24].

##### Upper-body muscular strength

The *arm curl test* involves determining the number of times a hand weight (2.3 kg for women) can be curled through a full range of motion in 30 s seconds [24]. Additionally, *handgrip strength test* will be measured using a digital dynamometer (TKK 5101 Grip-D; Takey, Tokyo, Japan) as described elsewhere [25]. The participants will perform (alternately with both hands) these tests twice. The best value of 2 trials for each hand will be chosen and the average of both hands will be used in the analyses.

##### Lower-body flexibility

The *sit and reach test* required the use of the sit-and-reach standardized box with a slide ruler attached to the top [26]. The participant will be required to sit with knees straight and legs together, and feet placed against the box. The participant slowly will reach forward as far as possible [26]. The final position that the participant reach in centimetres will be the test score. The best score of two attempts will be recorded. Additionally, the *back saver sit and reach test* will be carried out in the same sit-and-reach standard box described above. The participant will be required to sit with the untested leg bent at the knee and the tested leg with the knee straight and feet place against the box. The scoring is the same as the sit and reach test but only one leg is evaluated at a time. The best score of two attempts for each leg in centimetres will be recorded and the average of both legs will be used in the analyses.

